### Recruitment of subjects and time schedule

Community-dwelling older adults will be recruited through GP surgeries. The recruitment period starts in April 2009 and ends in July 2009. The last participant is expected to finish the intervention in November 2009. In order to recruit a representative sample, all participants are recruited consecutively through (approximately 10) GP practices (motivated research practices associated to the Institute of General Practice and Family Medicine, University Witten/Herdecke) within predetermined time periods. All patients aged 70 years or above who are seen by the GP within his consultation hours (personal contact) within that time period are screened for eligibility. Exclusion for medical or other reasons (see exclusion criteria) is documented. If the physician considers a patient eligible for the study, the patient is informed about the study in detail by the physician and by an exercise therapist. The therapist spends the whole recruiting period in the practice to assist the GP and to document the recruitment process. After a participant has given written informed consent, appointments for the baseline assessment (telephone interview and motor tests in the practice, see secondary outcome measures) are made. The recruiting period for the respective physician ends with the recruitment of a predetermined number of patients. The recruitment period for the first participating practice ends with the recruitment of 12 patients. The number of participants to be recruited by the following practices depends on the number of patients that have already passed the baseline assessment in the previous practices. The target of this recruitment mode is that 90 subjects participate in the baseline assessment (on average 9 patients per practice if 10 practices participate in the study).

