#### Home-based exercise programme

The exercise programme (described in section "Development of the exercise programme") consists of two main components that should be performed in alternating order:

1. a combination of home-exercises to improve strength, flexibility and balance on 3 days of the week,

2. walking to improve aerobic capacity on 4 days of the week.

Every participant is instructed and supervised by his personal exercise therapist. The exercise programme usually starts with a selection of a few simple home-exercises and with short walks. Additional exercises are taught by and by (depending on the participant's progress) with the advancement of the intervention. The duration of the walks is also increased in a stepwise manner. Days of rest are accepted according to the patient's needs. In case a participant is able to perform all home-exercises, he performs ten strengthening exercises (moderate intensity 5–6/10), followed by four flexibility exercises and two balance exercises. The exercises are numbered and should always be performed in the same chronological order. To perform all home-exercises in a row it takes about 30 to 45 minutes. In case of questions or problems concerning the exercise programme, patients have the opportunity to contact their GP or their exercise therapist.

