#### Criteria to decide on preparation of an RCT

In order to decide for or against the conduction of a randomised controlled trial on the new programme, three criteria based on primary outcome measures (see previous subsection) were set up. If one of them is met, the plans for an RCT will be cancelled:

**Criterion 1**. In the subsequent appraisal interview, more than 50% of participating GPs answer "no", when asked if they once again would participate in the trial, and the reasons for this answer seem unchangeable.

**Criterion 2**. More than 30% of the participants have to stop exercises for medical reasons, which the physician judges to be probably caused by the intervention.

**Criterion 3**. The adjusted drop out rate (see section "primary outcome measures – measures of drop-out") is above 60%, and no simple change of the criteria would clearly level down the adjusted drop out rate.

These three requirements will be analysed using binomial tests.

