#### Sample size

There are 3 criteria to decide if an RCT should be conducted. The power calculation is based on criterion 3, that means the adjusted drop out rate should be less than 60% to conduct an RCT. We expect more than half of the patients to actually complete the exercise programme and therefore assume a drop out rate of 45%. Given these assumptions a sample size simulation for a binomial test results in 90 patients (power = 80%, alpha = 5%).

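### The binomial tests and the sample size of 90 assume independent patients although recruitment is by practice; stated alpha and power should be shown over an ICC range, with a practice-clustered sensitivity analysis for criteria 2 and 3

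*Protocol article*

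**What the plan says.** The section *Criteria to decide on preparation of an RCT* lists three criteria, any one of which would cancel the RCT. Criterion 1 counts GPs who would not take part again (more than 50%). Criterion 2 counts participants who stop for medical reasons that the physician attributes to the intervention (more than 30%). Criterion 3 is an adjusted drop-out rate above 60%. The method is fixed in one sentence: "These three requirements will be analysed using binomial tests".

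The *Sample size* section rests on criterion 3: "the adjusted drop out rate should be less than 60% to conduct an RCT". It assumes a true rate of 45% and reports "a sample size simulation for a binomial test results in 90 patients (power = 80%, alpha = 5"%). Neither section mentions practice, clustering, an ICC or a design effect.

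Under *Recruitment of subjects and time schedule*, "all participants are recruited consecutively through (approximately 10) GP practices", with 12 patients in the first and "on average 9 patients per practice if 10 practices participate in the study". The practice's GP gives medical clearance (*Inclusion criteria*), decides on eligibility (*Risk-benefit considerations*) and judges whether an event was caused by exercise and whether the patient may go on (*Documentation of any undesirable event during the intervention*). On the therapist, *Home-based exercise programme* says: "Every participant is instructed and supervised by his personal exercise therapist". The number of therapists, and how they are allotted to practices, is not stated.

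**The concern.** A binomial test takes every patient as an independent draw with the same probability. Here patients come in blocks with a common GP and practice, and the second aim of the study is to evaluate the cooperation between GP and therapist, which operates at practice level. It is plausible that willingness to continue, and the GP's verdict on whether a medical stop was due to exercise, differ between practices. If they do, the variance of the observed proportion is larger than the binomial variance.

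At stake is the decision to commit resources to an RCT. With between-practice variation, a programme whose true drop-out is at the unacceptable 60% passes more often than planned, and one with 45% passes less often. The article states the test and the power itself, so this is not a detail left to an analysis plan.

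**Working it through.** **Inputs.** From *Sample size*: p0 = 0.60, p1 = 0.45, n = 90, power 80%, alpha 5%, sidedness not stated. From *Recruitment*: about 10 practices, 12 patients in the first, 9 on average. Assumed: ICC (ρ) of 0.01 to 0.10; practice sizes 12, six of 9 and three of 8 (12 + 54 + 24 = 90); all 90 patients in the adjusted set.

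**Step 1: the plan's own figure.** Exact binomial test with at most 2.5% per tail. With X drop-outs among 90:
- P(X ≤ 44 | 0.60) = 2.13% and P(X ≥ 64 | 0.60) = 1.90%, so total size is 4.03%.
- P(X ≤ 44 | 0.45) = 80.2%.
- Under this rule 90 is the smallest n with power of at least 80% (n = 88 gives 79.9%, n = 89 gives 76.9%).

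A one-sided 5% exact test reaches 80% at n = 71, or at 75 if power is to stay at or above 80%. The stated 90 is therefore the two-sided exact test with independent patients.

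**Step 2: loss of information.** Design effect DE = 1 + (Σm²/Σm − 1)ρ. Here Σm² = 144 + 486 + 192 = 822 and 822/90 = 9.13, so DE = 1 + 8.13ρ.

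**Step 3: the same rule with variation between practices.** Each practice's drop-out rate follows a beta distribution with mean p and ICC ρ. Its standard deviation is √(ρ·p(1 − p)). The beta-binomial counts are summed exactly over the 10 practices, and the cut-offs stay at 44 and 64.

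| ICC | SD of practice rates at 60% | DE | 90/DE | False-go tail (nominal 2.5%) | Total error | Power at 45% |
|---|---|---|---|---|---|---|
| 0 | 0 | 1.00 | 90 | 2.1% | 4.0% | 80.2% |
| 0.01 | 4.9 points | 1.08 | 83 | 2.6% | 4.9% | 79.3% |
| 0.02 | 6.9 points | 1.16 | 77 | 3.0% | 5.7% | 78.4% |
| 0.05 | 11.0 points | 1.41 | 64 | 4.4% | 8.4% | 76.3% |
| 0.10 | 15.5 points | 1.81 | 50 | 6.7% | 12.9% | 73.6% |

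The false-go tail is the chance of 44 or fewer drop-outs when the true rate is 60%. Ten practices of exactly 9 give nearly the same results (total error 12.8% at ICC 0.10).

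**Step 4: hold the false-go tail at 2.5%.** The cut-off must fall to 43, 42 and 41 at ICC 0.02, 0.05 and 0.10. Power is then about 72%, 64% and 56%. Part of the drop comes from the discreteness of the counts: at cut-off 43 and ICC 0.02 the actual tail is 1.9%.

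**Step 5: criterion 2.** The article gives no expected rate and no power for it, so no size can be worked out. The independence assumption is the same.

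**The case against.** **The ICC is not in the documents.** True: the whole size of the effect is conditional. At 0.01 it is negligible, because the exact test has slack (4.0% used of 5%). A reader might infer that the stated 5% and 80% fail outright. The documents do not support that; they fail only if practices differ enough.

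**The answer depends on sidedness.** If 5% was meant one-sided, the cut-off is 45. The false-go error is then 4.6%, 6.3% and 8.9% and power 83.7%, 81.4% and 78.4% at ICC 0.02, 0.05 and 0.10. Both stated properties survive at 0.02. But that reading does not yield 90. One-sided error must not be set beside two-sided power, since the two belong to different cut-offs.

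**A shared therapist is not stated.** It is tempting to read one therapist per practice into the text, but this is only implied. One therapist could serve several practices, and correlation would then cross practices. The shared GP and practice are enough for the point.

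**Criterion 3 leaves out medical stops.** Correct: the adjusted set removes them, so the GP's judgement on stopping bears on criterion 2. For criterion 3 the argument rests on practices differing in voluntary drop-out.

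**A practice-level test would cost too much.** This stands against replacing the binomial test. A two-sided t-test on practice proportions has power from about 65% at ICC 0.02 down to 46% at 0.10. Restoring 80% with practices of 9 and a reset cut-off takes 108 to 162 patients. A wrong cancellation is also a harm.

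**The decision is not a pure test.** Criteria 1 and 3 carry judgement clauses, so the rates above describe the test and not the full decision. Nor does the article rule out looking at practices: practice profile data are collected and exploratory analysis is planned. It would go too far to say that practice variation is lost.

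**Conclusion.** The point holds in conditional form. The binomial tests for criteria 2 and 3, and the 90, assume independent patients, and the 90 has no allowance for practice. Under the rule that reproduces it, total error goes from 4.0% to between 4.9% and 12.9%, the false-go tail from 2.1% to between 2.6% and 6.7%, and power from 80.2% to between 79.3% and 73.6%, over assumed ICCs of 0.01 to 0.10. The departure is trivial at the lower end and matters from about 0.02 to 0.05 upward.

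This assumes beta-distributed practice rates, practice sizes as listed, all 90 patients in the adjusted set, and practices viewed as a sample from those a later RCT would use. That view fits the purpose of the study. For criterion 2 the concern is one of principle only, without a figure. Criterion 1 has the GP as its unit and is not affected.

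**What to change.** 1. In *Sample size*, state the test as two-sided if that was intended, say that 80% power and 5% alpha hold only if patients are independent, and restate both over an ICC range such as 0.01 to 0.10.
2. Keep the binomial test, but add for criteria 2 and 3 a 95% confidence interval that respects practice, or a sensitivity analysis (beta-binomial, or based on practice-level proportions). Say in advance that it will be considered in the decision on the RCT.
3. Report the ICC for drop-out with its confidence interval, labelled as imprecise planning information. With about 10 practices of 9 and a true ICC of 0.05, the estimate ranges from about −0.07 to 0.22 in 95% of simulated studies.
4. State how therapists are allotted to practices, so that the level of clustering is clear.

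The cost is some wording and one added analysis of data already collected. Intervals will be wider and the stated power lower. No extra patients are needed.

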#### Data exploration

Additionally, explorative data analysis will be performed to estimate the effects of the programme, to detect shortcomings and perhaps to identify certain subgroups with contrary results or special problems.

#### Individual feedback

Each participant will receive a structured feedback on his or her personal results. GPs will be handed out aggregated results.

#### Sample size

There are 3 criteria to decide if an RCT should be conducted. The power calculation is based on criterion 3, that means the adjusted drop out rate should be less than 60% to conduct an RCT. We expect more than half of the patients to actually complete the exercise programme and therefore assume a drop out rate of 45%. Given these assumptions a sample size simulation for a binomial test results in 90 patients (power = 80%, alpha = 5%).

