##### Measures of drop-out

For each case of discontinued participation, the following reasons will be discriminated: medical reason (*r*_1_), change or misjudgement of inclusion or exclusion criteria (*r*_2_), subject's own decision (*r*_3_). After that, certain sets (groups) will be aggregated:

*A *– all participants who passed the baseline assessment

*DO*_*i *_– participants who drop out by reason *r*_*i*_

*DO *= *DO*_1 _∪ *DO*_2 _∪ *DO*_3 _– all participants who drop out

*A** = *A*\(*DO*_1 _∪ *DO*_2_) – adjusted set of participants (all participants not constrained to abort exercise by medical or trial criteria reasons)

*DO** = *A** ∩ *DO*_3 _– adjusted drop out group (participants who discontinue on their own decision). Members of this group will be asked for a personal reason (voluntary and open question), and also be asked to participate in the final assessment.

The following parameters are of special interest:

|*DO*| – total number of participants who drop out after the initial assessment

|*DO*_*i*_| – number of participants who discontinue for reason *R*_*i *_

|*DO**|/|*A**| – adjusted drop out rate

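### The stated 80% power for criterion 3 assumes that all 90 baseline patients are in the denominator and uses a 45% rate derived from overall completion, whereas criterion 3 is defined on the smaller adjusted set

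*Protocol article*

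**What the plan says.** The Sample size section ties the calculation to one criterion: "The power calculation is based on criterion 3, that means the adjusted drop out rate should be less than 60% to conduct an RCT". The planning rate follows: "We expect more than half of the patients to actually complete the exercise programme and therefore assume a drop out rate of 45" per cent. The result is "Given these assumptions a sample size simulation for a binomial test results in 90 patients (power = 80%, alpha = 5" per cent).

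Under Measures of drop-out, the starting set `A` is "all participants who passed the baseline assessment". The set `A*` takes out everyone who stops for a medical reason or because an inclusion or exclusion criterion changed or was misjudged; it is the "adjusted set of participants (all participants not constrained to abort exercise by medical or trial criteria reasons"). The numerator `DO*` is the "adjusted drop out group (participants who discontinue on their own decision"). The adjusted rate is the size of `DO*` divided by the size of `A*`.

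The section on recruitment and time schedule sets the number entering the study: "The target of this recruitment mode is that 90 subjects participate in the baseline assessment". Under the criteria for deciding on an RCT, the method is given as: "These three requirements will be analysed using binomial tests".

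**The concern.** Two quantities are used as if they were the same, and this happens twice.

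The first is the denominator. Ninety is the number planned to pass baseline, which is the size of `A`. The test of criterion 3 is computed on `A*`, which is smaller than 90 as soon as one patient leaves for a medical or criteria reason. The article states no allowance for this step. Its own rules expect such losses: the two reasons have their own categories, and criterion 2 cancels the RCT only when more than 30% have to stop for medical reasons judged probably caused by the intervention.

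The second is the rate. The 45% is argued from the share of all patients expected to complete, which describes total drop-out, but it is used as the planning value for the adjusted rate.

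Criterion 3 is the only criterion with a power calculation, and meeting it counts towards cancelling the RCT. A reader who relies on 80% should be able to tell which test, denominator and rate that figure belongs to.

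**Working it through.** **Inputs.** Threshold rate 0.60, planning rate 0.45, 90 patients, power 80%, alpha 5%, binomial test (Sample size). Definitions of `A`, `A*` and `DO*` (Measures of drop-out). Target of 90 at baseline (recruitment section). The share d removed between `A` and `A*` is not in the article; 5%, 10% and 20% are assumptions.

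**Formula.** For n patients in the denominator, let c be the largest count with P(X ≤ c; n, 0.60) ≤ 0.025 (two-sided 5%, equal tails) or ≤ 0.05 (one-sided 5%). Power is P(X ≤ c; n, p1), where p1 is the true adjusted rate.

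**Reproducing the plan's figure.**
- Two-sided exact, n = 90: c = 44, lower-tail size 0.0213, power 0.802. With equal tails, 90 is the smallest n that reaches 80%. The minimum-likelihood version of the two-sided exact test also gives 0.802 at 90; it first reaches 80% at 87 and stays there from 90 on.
- One-sided exact 5%, n = 90: c = 45, size 0.0347, power 0.855. It first reaches 80% at n = 71.
- Normal approximation: 85 two-sided (92 with continuity correction); 67 one-sided (74 with continuity correction).

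Of the variants tried, only the two-sided exact test gives 90 with 80%. It does so with all 90 in the denominator and p1 = 0.45.

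**Putting the defined denominator in.** The size of `A*` is 90 × (1 − d), rounded. If 45% is the adjusted rate, p1 stays at 0.45. If 45% is total drop-out, p1 = (0.45 − d)/(1 − d); for example, at d = 10%, 0.35/0.90 = 0.389.

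| Share removed (assumed) | Size of `A*` | Two-sided power, 45% is adjusted rate | One-sided 5% power, 45% is adjusted rate | Adjusted rate if 45% is total drop-out | Two-sided power at that rate |
|---|---|---|---|---|---|
| 0% | 90 | 80.2% | 85.5% | 45.0% | 80.2% |
| 5% | 86 | 79.5% | 85.1% | 42.1% | 91.5% |
| 10% | 81 | 75.3% | 81.7% | 38.9% | 96.5% |
| 20% | 72 | 69.1% | 76.9% | 31.25% | 99.8% |

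The two-sided columns use equal tails. Exact power moves in steps, so neighbouring sizes differ: on the adjusted reading it is 79.9% at 88 and 76.9% at 89. Averaging over a binomial size of `A*` smooths this: 77.4%, 74.3% and 69.0% at 5%, 10% and 20% removed with equal tails, and 78.8%, 76.0% and 71.6% with the minimum-likelihood version.

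**One-sided test, adjusted rate 45%.** The lowest power for any size of `A*` from 75 to 90 is 80.8%, at 75. At 74 it is 77.3%. The margin is therefore 90 − 75 = 15 removals.

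**The case against.** The strongest reply is that the plan may be conservative rather than short of power. Read literally, the 45% is argued from completion by all patients and so is total drop-out. The adjusted rate is then below 45% and two-sided power rises with losses, to about 91% at 5% removed and 96% at 10%. Further, no sidedness is stated and the decision is directional; a one-sided 5% test has 85.5% power at 90 and room for 15 removals. The settings of the simulation may stand in a fuller document. Small losses cost little even on the adverse reading: 79.5% at 86. Finally, cancellation under criterion 3 also requires that no simple change of the criteria would clearly lower the rate, and this is a single-arm feasibility study.

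All of this stands against a claim that the trial is underpowered, and it lowers the weight of the point. It does not remove the mismatch. On the total-drop-out reading the two-sided power is well above 80% once patients are removed, and one-sided it is already above 80% at 90, so neither reading makes the stated 80% the power of the test as defined.

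A reader might also infer that the plan contradicts its own expectation about completion, because an adjusted rate of 45% with 10% removed leaves 0.90 × 0.55 = 49.5% completing. That rests on the assumed 10%: at 5% removed the figure is 0.95 × 0.55 = 52.25%. With no removal share in the article, there is no contradiction.

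**Conclusion.** The point holds as a mismatch of definitions; the binomial arithmetic itself reproduces. The stated 80% belongs to a two-sided exact 5% test with 90 patients in `A*` and an adjusted rate of 45%, whereas the plan brings 90 into `A` and argues the 45% from overall completion. With 10% or 20% removed, two-sided power is about 75% or 69% if 45% is the adjusted rate; with 10% removed it is about 96% if 45% is total drop-out. These figures rest on the assumed shares and on a two-sided test inferred from reproducing the 90.

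It is tempting to conclude that criterion 3 lacks adequate power. The article does not support that: the direction of the error depends on which rate the 45% is, and a one-sided test would absorb moderate losses. The point is worth correcting because the figure backs the only powered decision rule, but it is not a defect that must stop the trial.

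**What to change.** In the Sample size section:

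1. State whether the 45% is the adjusted rate or total drop-out. If it is total drop-out, convert it with (0.45 − d)/(1 − d).
2. Give an expected share d of medical and criteria drop-outs, and compute and restate the power on the expected size of `A*` instead of on 90.
3. Declare the go/no-go test of criterion 3 one-sided at 5%, which suits a decision that runs in one direction. With an adjusted rate of 45%, power stays at or above 80% as long as no more than 15 of the 90 are removed. If more are expected, report the lower figure (76.9% at 72).

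The cost is a rewritten paragraph. No extra patients are needed. The downside is either a restated power figure, less favourable if the test stays two-sided and 45% is the adjusted rate, or acceptance of a one-sided 5% error rate.

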### Ethical approval

The research carried out will be in compliance with the Helsinki Declaration. The protocol has been approved by the Ruhr-University of Bochum (Germany) Ethics Committee on 10 February 2009 (Reg.-No. 3054-07).

## Discussion

We conceptualised an activity programme for community-dwelling seniors, which

• on the individual level, contains multidimensional exercises according to accepted guidelines, and

• on the institutional level, establishes a cooperation between general practitioners and exercise therapists.

From the methodological point of view, clear criteria for the decision on the next step of development are given: A randomised controlled trial as phase III makes sense, if and only if phase II level of development was successful. Otherwise, the programme has to be changed fundamentally and phase II has to be passed through again. While the training effectiveness and patient eligibility are not expected to turn out as problems, another aspect may be crucial: The adherence of initially motivated participants. Both the design of the programme and the trial emphasise this aspect. The authors also were assured by a study of Armit and coworkers [61], which appeared after planning the trial: Inactive patients (50–70 years of age) from two GP practices were randomised into three groups, for behaviour change advice by the physician, or by the physician in collaboration with an exercise scientist. The third group received collaborative advice and a pedometer. Self-reported physical activity time increased for all groups, but the most intense intervention (collaborative advice and pedometer) yielded the highest probability for the patients to meet physical activity guidelines. In summary, a home-based exercise programme, approaching and supporting community-dwelling but mobility-restricted seniors via their GP ("surgery approach") and an exercise therapist, is object of research with regard to feasibility and acceptance. In case of success, a randomised controlled trial should examine the effects of the programme. After positive evaluation, a future implementation within primary medical care may take advantage from the flexibility and individuality of the programme.
